## Methods

### Trial Design

This study will use a robust, pragmatic, 2-arm parallel group cluster randomized, active-controlled, noninferiority trial design. This study will be reported according to the CONSORT (Consolidated Standards of Reporting Trials) guidelines on reporting of noninferiority trials [13]. Study communities will be randomized into test or control groups by a central study coordinator through a computer-generated block randomization procedure, stratified by expected decay experience and exposure to community water fluoridation levels based on findings from our earlier work in the Kimberley region [6]. Both arms of the study will be provided with dental care; the control arm will be treated using the ART and HT approach, and the test arm will be treated using AgF. The test group will be further randomized into 2 groups via computer-generated allocation in concealed envelopes at study sites to receive 1 of the 2 AgF formulations. One formulation will have 38% AgF and KI as a staining reducing agent (Riva Star Aqua; SDI Limited); the other formulation will have 40% AgF with stannous fluoride as a reducing agent (Creighton Dental AgF; Whiteley Corporation). The Riva Star Aqua group will be further randomized to receive KI or no KI to evaluate KI’s effect on reducing the staining associated with AgF and evaluate its impact on caries arrestment. Moreover, we will evaluate the COHRQoL [14] and child dental anxiety and undertake an economic evaluation of the interventions. Focus group interviews, using the yarning approach, will be conducted to better understand the impact of the dental treatments [12]. We will also test the effectiveness of teledentistry in caries diagnosis and treatment prescription. Participants will have digital images taken of their dentition with a smartphone using standardized procedures [15]. The images will be stored and sent securely to a calibrated assessor at a remote site. The assessor, blinded to group allocation, will evaluate the images and diagnose and prescribe treatment.

### Study Setting

The interventions will be undertaken in remote community settings using mobile portable equipment in the Kimberley region of Western Australia. Because of the small population in the participating communities and to ensure confidentiality of participant information, the list of study sites will not be made available. The communities selected for inclusion in the study generally do not have ready access to dental care and may have to travel long distances by road to obtain care because care providers are not usually available in the community.

### Eligibility Criteria

Communities that participated in an earlier study will be invited to participate via community consultations with the community chair and community council [6]. Children aged between 6 months and 7 years, with or without dental caries, will be eligible. Children with complex medical conditions or developmental syndromes requiring specialist care or those with a need for urgent dental care will be excluded (those requiring urgent care will be referred to their local service provider).

### Ethical Considerations

This study received ethics approval from the Western Australia Aboriginal Health Ethics Committee (1348) and the University of Western Australia Human Research Ethics Office (2024/ET000760). A 2-stage consent process will be used. First, informed community consent will be obtained from the community to participate in the study. After community consent, individual signed informed consent will be obtained. The research team’s Aboriginal research assistant will assist parents and guardians by explaining the study to those whose first language is not English. Each participating parent and carer will be provided with a local community store voucher worth Aus $50 (US $32) as compensation for their time. Confidentiality of participant information will be protected by storing information on password-protected computers that are locked in offices accessible only to research personnel. Analysis will be undertaken on deidentified data.

### Interventions

#### Explanation for the Choice of Comparators

The primary comparison group is composed of the children who were provided with the minimally invasive treatment approaches, encompassing the ART [16] and the HT stainless steel crowns [17]. The ART and HT approach has been tested in remote communities and has been found to be an effective and feasible approach to delivering dental care in remote communities [6,18]. The secondary comparison is that of teeth treated with AgF with or without KI to evaluate the stain-reducing potential of KI.

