**For Riva Star Aqua**
Remove food debris and plaque by brushing with a toothbrush (no toothpaste).Isolate teeth to be treated with cotton rolls and gauze and apply petroleum jelly to the gingiva and lips.Dry the affected tooth surfaces and at-risk tooth surfaces to be treated with cotton pledgets.Dispense 0.05 mL AgF; bend the microbrush applicator and dip the tip of the applicator into the agent.Apply the agent with the microbrush onto the decayed surface and rub gently, maintaining contact with the tooth for 60 seconds; apply the agent also to at-risk, non-decayed surfaces for 60 seconds and remove excess from all surfaces with cotton pledgets.For tooth surfaces assigned to receive potassium iodide (KI), dispense 0.1 mL KI; using a new microbrush, dip the brush tip into the agent and apply to the decayed surface until precipitate forms. Then, reapply the agent until no precipitate forms, with 5- to 10-second intervals between reapplications.Place Orabase adhesive (Colgate Oral Pharmaceuticals, Inc) onto AgF-treated decayed surfaces, with or without KI.Advise participant to refrain from eating or drinking for 30 minutes after treatment.

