### Assignment of Interventions: Allocation

#### Sequence Generation

Communities will be allocated to intervention or control groups through computer-generated block randomization, stratified based on the estimated caries prevalence and community water fluoridation levels within communities. Communities will be assigned to the intervention or the control group after receiving community consent. Individual children in the intervention group will be further allocated into AgF treatment or AgF and KI treatment via sealed envelopes containing computer-generated block randomization. The envelopes will be opened by the project coordinator at the community study site, and they will assign each child at enrollment.

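### Trial Design randomises three AgF regimens, but the allocation sections and objective 3 know only two, so the KI contrast is not pinned to one product and its 84% power does not fit the nested design

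*Protocol article*

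**What the plan says.** Trial Design sets out a nested scheme. First, "The test group will be further randomized into 2 groups via computer-generated allocation in concealed envelopes at study sites", one group per AgF formulation. One formulation is 38% AgF (Riva Star Aqua); "the other formulation will have 40% AgF with stannous fluoride as a reducing agent". Then "The Riva Star Aqua group will be further randomized to receive KI or no KI to evaluate KI’s effect on reducing the staining", and the same sentence adds the effect on caries arrest as a second purpose. The result is three regimens: 38% AgF with KI, 38% AgF without KI, and 40% AgF with stannous fluoride.

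Textbox 1 fits this scheme. The KI step stands only in the Riva Star Aqua procedure ("For tooth surfaces assigned to receive potassium iodide (KI), dispense 0.1 mL KI"). The Creighton procedure has its own stannous fluoride step and no mention of KI.

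The sections that govern allocation say something else. Sequence Generation: "Individual children in the intervention group will be further allocated into AgF treatment or AgF and KI treatment via sealed envelopes". Implementation repeats this two-way split. Neither mentions a product.

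The same pair of groups appears in objective 3, in the timeline (Table 1), in the colour assessment under Plans for Assessment and Collection of Outcomes, and in Explanation for the Choice of Comparators: "The secondary comparison is that of teeth treated with AgF with or without KI to evaluate the stain-reducing potential of KI".

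Sample Size gives 84% power for a 20% difference in caries arrest between lesions treated with and without KI. It does not say how many children are in each group or which two rates were used.

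**The concern.** A two-group scheme has no place of its own for a child on the 40% product. Such a child did not receive KI, so an analyst working from objective 3 and the allocation sections could reasonably file that child under AgF without KI. The 40% product is not a no-KI version of the 38% product: its AgF strength differs, and a reducing agent of its own is applied to the treated lesion. Only the randomised split inside the 38% product isolates KI.

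At stake are the one hypothesis on discoloration (objective 3) and the KI effect on arrest. The randomisation is also at stake, because a list built from Sequence Generation would differ from one built from Trial Design.

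**Working it through.** **1. The allocation texts side by side**

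| Section | Who is allocated | To what | Product step |
|---|---|---|---|
| Trial Design | Test arm, then the 38% product group | Product, then KI or no KI | Yes |
| Sequence Generation; Implementation | All intervention children | AgF, or AgF and KI | None |
| Objective 3; comparators; Table 1; colour assessment | Not an allocation text | AgF with or without KI | Not named |

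The first two rows cannot both describe the child-level randomisation.

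**2. What pooling would do, if it were done**

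Let A be the outcome rate on 38% AgF with KI, B the rate on 38% AgF without KI, and C the rate on the 40% product. Let s be the share of 40%-product children in a pooled no-KI group. Then

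A − [(1 − s)B + sC] = (A − B) + s(B − C).

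The first term is the KI effect. The second is the distortion from the product difference. The document gives neither s nor B − C, so the sign and size of the distortion are unknown. It is zero if the 40% group is kept apart.

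**3. The stated 84%**

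Inputs from Sample Size: 320 per arm enrolled, 25% loss in each of two years, α = .05, rates of 61% and 81%. Assumptions: two-sided test, equal splits, one unit per child, no design effect (children are randomised individually), and 61% vs 81% as the 20-point pair.

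Evaluable test arm: 320 × 0.75² = 180, the article's own figure.

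Power = Φ{ [ |p₁ − p₂|√n − 1.96√(2p̄(1 − p̄)) ] / √(p₁(1 − p₁) + p₂(1 − p₂)) }, with p̄ = 0.71, so √(2 × 0.71 × 0.29) = 0.642 and √(0.2379 + 0.1539) = 0.626.

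- All 180 split in two, n = 90 per group: (0.20 × 9.487 − 1.258)/0.626 = 1.02, power **84.7%**. This reproduces the stated 84%.
- Nested scheme, 180/2/2 = 45 per group: (0.20 × 6.708 − 1.258)/0.626 = 0.13, power **55.3%**.
- 40% product pooled into no KI, 45 vs 135: 71% to 76%, depending on which group has the higher rate.

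**4. Sensitivity to the unstated rates**

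| 20-point pair | 90 vs 90 | 45 vs 45 |
|---|---|---|
| 50% vs 70% | 78.7% | 49.0% |
| 61% vs 81% | 84.7% | 55.3% |
| 71% vs 91% | 93.4% | 68.2% |
| 79% vs 99% | 99.3% | 87.1% |

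With 45 per group, a figure near 84% needs rates close to the ceiling.

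**The case against.** The best defence is that Trial Design already settles the matter. It fixes the population (38% product), the randomised contrast and both purposes. Textbox 1 agrees: its own use of the phrase, "onto AgF-treated decayed surfaces, with or without KI", occurs in the Riva Star Aqua procedure only. On that view the sentence on comparators is a one-line summary, the colour assessment only describes a measurement, Table 1 is only a timeline, and exact analysis sets belong in an analysis plan that is not shown.

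Most of this stands. The within-product contrast is probably what is intended, and no section orders pooling. A reader might infer that the protocol places the stannous fluoride product in the no-KI group, that two thirds of that group would then be on another product, and that the KI effect could reverse. The document does not support that. Two thirds (160 of 240) needs assumed equal splits under the nested scheme, combined with a comparator that ignores the purpose stated for that scheme. Read literally, Sequence Generation with equal allocation would give 160 vs 160. A reversal needs staining rates that appear nowhere in the article. Nor does the text let a site choose the product freely: Sequence Generation omits the product step, but Trial Design randomises it.

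The defence does not explain the allocation sections. Sequence Generation and Implementation are not shorthand for an analysis. They state who is randomised to what, and they contradict Trial Design. This is a conflict between printed statements, so neither article length nor an unseen analysis plan accounts for it.

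**Conclusion.** The concern holds as an inconsistency that leaves the KI contrast open to product confounding. It does not hold as a demonstrated bias. Two incompatible child-level randomisations are described, and objective 3 is worded to fit the one that does not isolate KI.

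The quantifiable part is power. At 61% vs 81% the stated 84% matches the whole evaluable test arm split 90 vs 90, whereas the nested scheme gives about 45 vs 45 and about 55%. Across 20-point pairs from 50/70 to 79/99, the nested power runs from 49% to 87%. This rests on equal splits, a two-sided test and one unit per child. Because the article does not state the KI and no-KI rates, the match at 90 vs 90 suggests, but does not prove, that the sample-size text counted the whole test arm. The 84% concerns arrest; no power is given for discoloration.

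The point should be settled before recruitment, planned for March 2026.

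**What to change.** 1. Rewrite Sequence Generation, Implementation and Table 1 to match Trial Design, with one child-level allocation list that names both product and KI status, and state the allocation ratios.
2. Word objective 3, the comparator section and the colour assessment so that the KI analyses, for discoloration and for arrest, compare KI with no KI among children randomised within the 38% product.
3. Report the 40% AgF and stannous fluoride group as its own category, not within no KI.
4. Restate the KI power with the group sizes and the two rates used.

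The cost is wording and one analysis-set definition; no extra children or data are needed. The drawback is a smaller KI contrast, about 45 vs 45 evaluable with equal splits, and a lower stated power unless the expected rates lie near the ceiling.

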#### Intervention Description

Children allocated to the test group will be provided with AgF, either Riva Star Aqua (38% AgF and KI) or Creighton Dental AgF (40% AgF and stannous fluoride). Only the primary molars will be included. The AgF will be applied by an Aboriginal health practitioner or worker who has been trained in the application of fluoride agents. The agents will be applied once only, after baseline assessment, and repeated at the 12- and 24-month follow-ups. All other treatments required beyond AgF application will be managed by the oral health practitioner team. Interventions for Riva Star Aqua and the Creighton AgF are outlined in Textbox 1.

Interventions for Riva Star Aqua and the Creighton silver fluoride (AgF).
**For Riva Star Aqua**
Remove food debris and plaque by brushing with a toothbrush (no toothpaste).Isolate teeth to be treated with cotton rolls and gauze and apply petroleum jelly to the gingiva and lips.Dry the affected tooth surfaces and at-risk tooth surfaces to be treated with cotton pledgets.Dispense 0.05 mL AgF; bend the microbrush applicator and dip the tip of the applicator into the agent.Apply the agent with the microbrush onto the decayed surface and rub gently, maintaining contact with the tooth for 60 seconds; apply the agent also to at-risk, non-decayed surfaces for 60 seconds and remove excess from all surfaces with cotton pledgets.For tooth surfaces assigned to receive potassium iodide (KI), dispense 0.1 mL KI; using a new microbrush, dip the brush tip into the agent and apply to the decayed surface until precipitate forms. Then, reapply the agent until no precipitate forms, with 5- to 10-second intervals between reapplications.Place Orabase adhesive (Colgate Oral Pharmaceuticals, Inc) onto AgF-treated decayed surfaces, with or without KI.Advise participant to refrain from eating or drinking for 30 minutes after treatment.
**For Creighton Dental AgF**
Remove food debris and plaque by brushing with a toothbrush (no toothpaste).Isolate teeth to be treated with cotton rolls and gauze and apply petroleum jelly to the gingiva and lips.Dry affected tooth surfaces and at-risk tooth surfaces to be treated with cotton pledgets.Dispense 0.05 mL AgF; bend the microbrush applicator and dip the tip of the applicator into the agent.Apply the agent with the microbrush onto the decayed surface and rub gently, maintaining contact with the tooth for 60 seconds. Apply the agent also to at-risk, nondecayed surfaces for 60 seconds and remove excess from all surfaces with cotton pledgets.Dispense 0.05 mL stannous fluoride. Using a new microbrush, dip the microbrush tip into the stannous fluoride solution and apply it to the decay-treated tooth surfaces.Place Orabase adhesive onto treated decayed surfaces.Advise participant to refrain from eating or drinking for 30 minutes after treatment.

Children allocated to the control group will be provided treatment by the oral health practitioner team (dental therapist and dental clinic assistant). Teeth to be restored using the ART approach will have the decayed tooth surfaces prepared using hand instruments only for caries removal without local anesthesia and teeth restored with a glass ionomer cement. Teeth restored using the HT will have the tooth surface cleaned, but caries will not be removed. The tooth will then be restored with a stainless-steel crown, cemented with a glass ionomer cement. The treating clinician will determine the type of restoration to provide for each control participant.

All the children will be reviewed at 12 and 24 months, and AgF treatments will be reapplied.

#### Criteria for Discontinuing or Modifying Allocated Interventions

Participants allocated to the test arm (AgF treatment) who request restorative care as per the control arm (ART and HT treatment) will be provided with the requested care. Similarly, control participants who request the test intervention will be provided with the test intervention. The reasons for the request will be noted. All participants will be analyzed on an intention-to-treat and per-protocol basis.

#### Strategies to Improve Adherence to Interventions

All participants will be provided with information and guidance on oral health care procedures. No specific actions are required from the participants beyond oral hygiene measures to maintain oral health.

#### Relevant Concomitant Care Permitted or Prohibited During the Trial

All participants will be able to access and receive regular dental care from their usual dental care provider. Information regarding treatment received during the follow-up interval will be sought from participants at each follow-up.

#### Provisions for Posttrial Care

All participants will be provided with contact details of the researchers to report any adverse events that may arise after the intervention.

### Outcomes

The primary outcome of interest is the number of treated decayed teeth at baseline that became arrested at each follow-up period and the number of sound surfaces treated at baseline that became carious at follow-ups, measured by the count of decayed, missing, and filled tooth surfaces. Secondary outcomes will be changes in COHRQoL and child dental anxiety (Table 1).

**Table 1 table1:** Standard Protocol Items: Recommendations for Interventional Trials (SPIRIT) participant timeline.

SPIRIT participant timeline		Enrollment	Allocation	After allocation			Closeout
		–T1^a^		Baseline	12 mo	24 mo	

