**Methods:**

This study is a cluster-randomized controlled trial with communities randomized and stratified based on caries level and water fluoridation status. The trial will recruit 640 children (aged between 6 months and 7 years) from 30 communities. Informed consent will be obtained. At baseline, each child in the intervention group will be examined by a calibrated examiner and subsequently by an oral health practitioner who will prescribe to an Aboriginal health practitioner the teeth to be treated with AgF. A formulation with 38% AgF will be applied for 1 minute (0.004 mL per tooth). The control group will be provided with standard minimally invasive care. Participants will be followed annually for 2 years to assess caries arrest and prevention by blinded calibrated examiners. Child oral health–related quality of life and dental anxiety will be elicited through validated questionnaires. Tests of proportions will be used to evaluate the proportion of lesions arrested and the proportion of surfaces at risk that decayed over the follow-up. Multiple logistic regression with appropriate control for clustering of teeth and communities will be used to evaluate caries arrest, controlling for potential confounding factors.

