### Recruitment

Strategies used in the recently (successfully) completed study in the Kimberley region will be adopted, with further community engagement undertaken to refine and develop the research protocol with the community leaders. Participant recruitment will commence after obtaining community consent to participate. Participant recruitment and retention strategies will include (but not be limited to) personal contacts by the project coordinator and the Aboriginal research assistant and engagement via the media (radio and television); website; local agencies, such as the community offices, the local school or schools, child care centers, community health and nursing centers; posters and flyers at local community stores, and word of mouth via the community and the AAC.

Parents of eligible children expressing an interest in participating will be provided with an information sheet, and the study will be explained by the Aboriginal research assistant. Upon receipt of signed consent, each parent will complete a questionnaire (the Aboriginal research assistant will assist the parent to complete the questionnaire). A calibrated examiner will then undertake the baseline clinical examination and take digital images of the dentition using a developed protocol.

After the baseline examination, each child will be offered treatment as per the protocol for the group allocation. Efforts will be taken to provide comprehensive care, including extractions. From experience, we found that concurrent treatment of the child after the baseline examination offered the best option for care and reduced the likelihood of nonattendance at subsequent appointments. In addition, where extra capacity to deliver dental treatment is available, we will provide dental care to children not enrolled in the study as a community service. The CONSORT participant flowchart is shown in Figure 1.

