### Statistical Methods

#### Statistical Analyses for Primary and Secondary Outcomes

Analyses will be on an intention-to-treat and per-protocol basis. Objectives 1 to 3 will be tested using a test of proportions and logistic regression and negative binomial regression for overdispersed count data, accounting for clustering within individuals and communities. Subgroup objective 4 will be tested using paired tests for pre- and postintervention changes in COHRQol and dental anxiety as well as unpaired tests for between-group differences at baseline and follow-up; multivariable analyses will use generalized estimating equation linear regression to control for teeth and community clustering. Objective 5, economic analyses, will be tested as outlined in the subsequent section. All analyses will be undertaken by analysts who are blinded to group allocation status, and take into account clustering within communities and baseline factors and any baseline intergroup differences. Multiple imputations of missing data will be undertaken to evaluate its impact on the primary and secondary outcomes.

Objective 6 will be evaluated through qualitative analyses of the focus group interviews, with all interviews digitally recorded and independently transcribed. Transcripts will be read, and coding will be undertaken by analysts who are blinded to group allocation status. A thematic analytical approach will be adopted to develop themes and explore the contextual differences among the perceptions, experiences, and beliefs without a strict requirement for a theoretical focus [23,24]. Transcripts will be read multiple times to establish familiarity with the dataset. Two independent reviewers, one of whom will be an Indigenous researcher, will develop a coding scheme of the transcripts and also develop emerging themes. Where disagreement in coding is identified, the differences will be resolved through discussion and consensus. Our approach will broadly follow a reflexive thematic analysis (based on the study by Braun and Clarke [24]), drawing on subjective interpretations of both an Indigenous and a non-Indigenous researcher. The emergent themes will be explored and further refined. Data management will be facilitated using NVivo (version 12; Lumivero). Objective 7 will be evaluated by calculating sensitivity, specificity, predictive values, and receiver operating characteristics, validated against on-site clinical assessment.

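### The primary arrest outcome is restricted to treated decayed teeth, a denominator fixed after randomisation that conflicts at tooth level with Objective 1 and the stated intention-to-treat analysis

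*Protocol article*

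**What the plan says.** The protocol article's Outcomes section defines the first part of the primary outcome thus: "The primary outcome of interest is the number of treated decayed teeth at baseline that became arrested at each follow-up period". The second part carries the same condition: "the number of sound surfaces treated at baseline that became carious at follow-ups, measured by the count of decayed, missing, and filled tooth surfaces".

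Other sections are not restricted to treated teeth. Objective 1 (Objectives) counts teeth and surfaces with arrested lesions at baseline and follow-up. The section on discontinuing or modifying interventions states "All participants will be analyzed on an intention-to-treat and per-protocol basis", and the statistical methods section repeats "Analyses will be on an intention-to-treat and per-protocol basis".

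On timing, Sequence Generation assigns communities after community consent. Recruitment then places the baseline examination before treatment, after which "each child will be offered treatment as per the protocol for the group allocation". Concealment Mechanism says the clinical team and treating clinicians know the assignment. In the AgF arm the abstract refers to an "oral health practitioner who will prescribe to an Aboriginal health practitioner the teeth to be treated with AgF". In the control arm, Intervention Description leaves the type of restoration to the treating clinician. Recruitment adds that "Efforts will be taken to provide comprehensive care, including extractions".

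**The concern.** Receiving treatment is an event after randomisation. It can depend on the arm: the Background describes AgF as easy and painless to apply, whereas the control care needs caries removal with hand instruments or a crown, in children as young as 6 months. It can also depend on how severe the lesion is and how well the child cooperates, and both plausibly bear on arrest.

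A comparison limited to treated teeth asks how teeth fare once treatment has been delivered. Objective 1 and the intention-to-treat statement ask how the decay that children present with fares under each randomised care model. If untreated shares differ between arms, the two answers differ. Delivery is also part of the trial's principal aim, which includes feasibility, so failures to deliver treatment should not leave the primary result unnoticed.

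**Working it through.** **Step 1. Does the denominator matter?** In a count of arrested teeth per child, an untreated tooth adds zero and nothing is lost. But the abstract's methods test the proportion of lesions arrested, the Sample Size section compares two proportions, and the statistical methods section lists tests of proportions and logistic regression. These need a denominator, and the outcome definition offers treated teeth.

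**Step 2. Reproduce the planning figure.** Inputs from Sample Size: 61% and 81% arrest, power 80%, α 0.05, intracluster correlation (ICC) 0.09, 15 clusters per arm.
- Two-sided comparison of proportions: 80 per arm without and 90 with continuity correction, before clustering.
- Cluster size m = n(1 − ICC)/(K − n × ICC) = 90 × 0.91/(15 − 8.1) = 11.87, rounded up to 12. Then 15 × 12 = 180 per arm.
- Loss to follow-up: 180/0.75² = 320 per arm; 320/15 = 21.3, rounded up to 22 per cluster.

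The stated 180, 320 and 22 are reproduced. The 61% is a share of ART restorations, so the control planning rate also has a treated-teeth denominator.

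**Step 3. Size of the shift (assumed inputs).** Let uC and uA be the untreated shares of decayed teeth in the control and AgF arms. The protocol gives neither. Counting untreated teeth as not arrested,

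difference over all decayed teeth = 0.81(1 − uA) − 0.61(1 − uC),

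against 0.81 − 0.61 = 0.20 among treated teeth.

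| Control untreated | AgF untreated | AgF arrested | Control arrested | Difference |
|---|---|---|---|---|
| 5% | 0% | 0.810 | 0.580 | 0.231 |
| 10% | 2% | 0.794 | 0.549 | 0.245 |
| 20% | 5% | 0.770 | 0.488 | 0.282 |
| 2% | 5% | 0.770 | 0.598 | 0.172 |

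The shift is 0.61uC − 0.81uA, so it is zero when uA = (0.61/0.81)uC = 0.75uC and changes sign on either side of that.

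**Step 4. Sensitivity to the scoring rule.** If 20% of untreated teeth are arrested, the shift becomes uC(0.61 − 0.20) − uA(0.81 − 0.20).
- 5% v 0%: 0.05 × 0.41 = 0.021, a difference of 0.221.
- 2% v 5%: 0.02 × 0.41 − 0.05 × 0.61 = −0.022, a difference of 0.178.

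The shift is smaller, with the same direction.

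**Step 5. No difference among treated teeth.** With 61% arrest in both arms, and 20% of control and 5% of AgF teeth untreated, the all-teeth difference is 0.61 × 0.95 − 0.61 × 0.80 = 0.092 with no untreated tooth arrested, or 0.061 with 20% of them arrested. A treated-teeth analysis would report zero.

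**The case against.** The strongest reply is that this hangs on one word. The outcome is phrased as a number, negative binomial regression is planned for counts, and no section states a treated-teeth denominator for the analysis outright. Children who ask for the other arm's care receive it and are covered by the intention-to-treat statement. Treatment directly after the baseline examination is meant to limit non-attendance, and children needing urgent care are not enrolled. The group receiving neither form of care may therefore be small. If AgF is easier to deliver, restricting to treated teeth would tend to understate AgF, which is conservative for a noninferiority claim.

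Much of this stands as a limit on size. It does not remove the conflict: the proportion analyses need a denominator, the crossover provision does not cover teeth that receive nothing, and multiple imputation of missing data does not reach teeth outside the outcome definition. The conservative direction is plausible but not assured.

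Three stronger readings are tempting and not supported.
- A reader might infer that untreated control children are dropped, because "The primary comparison group is composed of the children who were provided with the minimally invasive treatment approaches". That sentence explains the choice of comparator. The analysis population is set elsewhere and covers all participants.
- A reader might infer that extracted teeth drop out. A tooth treated at baseline and later extracted still meets the definition, extraction is listed among the care provided, and missing surfaces are in the count. Their arrest status is simply not stated.
- A reader might take the all-teeth figures above as the true difference. They answer a different question, under assumed shares and a chosen scoring rule.

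**Conclusion.** The point holds at tooth level. As written, the primary arrest outcome is conditioned on a post-randomisation event determined differently in the two arms, and this must be reconciled with Objective 1 and the intention-to-treat statements. It does not show that the whole analysis departs from intention to treat.

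The size is unknown because the protocol gives no untreated shares. With the planning rates and untreated teeth counted as not arrested, untreated shares of a few percent move the 20-point difference by about 3 points: up to about 23 (5% control v 0% AgF) or down to about 17 (2% v 5%). The published sample size calculation is reproduced and is not called into question by this point.

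**What to change.** 1. For the intention-to-treat analysis, define the denominator as all eligible teeth with active decay at the baseline examination, analysed in the community's randomised arm whether or not they were treated.
2. Score untreated teeth by their observed status at follow-up, or as not arrested, and state which in advance.
3. Prespecify one rule for extracted teeth, with a sensitivity analysis under the alternative. Several rules are defensible; what matters is that one is fixed before outcomes accrue.
4. Keep the treated-teeth result as the per-protocol analysis.

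The comparator rationale needs no rewriting. The cost is a change of wording: the baseline examination precedes treatment and already records decay, so no new data are needed, and recruitment is planned to start only in March 2026. The downside is that arrest proportions may come out somewhat below the 61% and 81% used for planning, since the 61% is a share of restorations placed.
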